## Methods/design

The proposed study uses a 2 × 2 repeated-measures analysis of covariance (ANCOVA) design to evaluate the effects of 5 weeks of CWMT, adaptive versus ‘active control (fixed low level)’ training, as assessed by the improvement index (generated from task performances within the CWMT), neurocognitive testing, BOLD-fMRI measurements, cerebrospinal fluid neuroinflammatory proteins, monoamine, and metabolite levels. We propose to enroll 60 HIV-infected individuals and 60 seronegative healthy participants, with 30 adaptive and 30 active-control-training subjects randomized in each group (Fig. 1). HIV-positive and seronegative subject groups will be matched by age, sex, education, socioeconomic status, and cognitive status (matched by global cognitive score from the seven cognitive domains tested), as well as other co-variates (e.g., nicotine smoking and other substances abused). Based on the initial screening evaluations, subjects who fulfill all study criteria will be scheduled for a baseline neuropsychological evaluation, MRI-fMRI scans, and a lumbar puncture.

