### Participants

Subjects will be recruited via flyers, referrals from local HIV clinics, by word of mouth, or from ongoing studies. Potential research subjects will be screened by telephone or on-site, before being scheduled for a detailed out-patient evaluation at the UH-QMC MR Research Center at the Queen’s Medical Center in Honolulu, Hawaii.

In our pilot studies, we observed effect sizes from 0.7 to 1.2 for pre versus post CWMT in HIV-positive subjects in four of the working memory tests. We will need to enroll ≈ 17 HIV-positive subjects to detect an effect size of 0.7 for 80 % power (two-sided test). Effect sizes for BOLD signal change (pre versus post adaptive CWMT (0 and 1-back)) were 0.58–1.5 in the pilot HIV-positive subjects; at least 26 HIV-positive subjects are needed to detect an effect size of 0.58 for 80 % power (two-sided test). Since we encountered an ≈ 15 % (13 % in HIV and 20 % in the seronegative group) attrition rate in our pilot study, we propose to enroll 30 HIV and 30 seronegative subjects per training group to ensure adequate power, for a total of 120 subjects (60 HIV, 60 seronegative). Based on our experience, we will have to screen ≈ 500 individuals initially by telephone and 200 of these potentially eligible participants in person to have ≈ 150 subjects who will fulfill our study criteria, and complete the baseline evaluation. We expect that only ≈ 120 subjects (60 HIV and 60 seronegative) will follow through and be randomized for the training. We also expect that only 85 % (*n* = 102, 50 HIV and 52 seronegative) will return for the 1 month follow-up and only 80 % of these (*n* = 86, 40 HIV and 42 seronegative) will return to complete the 6-month follow-up evaluations. Furthermore, we expect that ≈ 20 participants who completed the ‘active control’ training will want to continue with the ‘adaptive training’ (Fig. 1).

HIV-infected participants must meet the following inclusion criteria: (1) men or women of any ethnicity, ages ≥ 18 years and able to provide informed consent; (2) HIV seropositive (with documentation from medical records); (3) stable on an antiretroviral regimen for 6 months or will remain without antiretroviral treatment during the duration of the CWMT study.

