Seronegative healthy participants must meet the following inclusion criteria: (1) men or women of any ethnicity, ages ≥ 18 years and able to give informed consent; (2) seronegative for HIV (to be confirmed by an HIV ELISA blood test if screened positive with ClearView® COMPLETE HIV-1/2 test).

Exclusion criteria for all subjects are: (1) history of co-morbid psychiatric illness that might confound the analysis of the study (e.g., schizophrenia, obsessive-compulsive disorder, major depression, or bipolar disorder); (2) confounding neurological disorder (e.g., multiple sclerosis, Parkinson’s disease, non-HIV brain infections, neoplasms, cerebral palsy, or significant head trauma with loss of consciousness >30 minutes); (3) significantly abnormal screening laboratory tests (>2 standard deviations) that might indicate a chronic medical condition (e.g., diabetes, severe cardiac, renal or liver disorders) that might affect brain function; (4) medications that could significantly alter functional brain imaging studies; (5) current or history of drug dependence within the previous 2 years, including amphetamines, cocaine, alcohol, and opiates, according to DSM-V dependency criteria (past casual or recreational usage will not be excluded); (6) positive urine toxicology screen (methamphetamine, amphetamine, cocaine, marijuana, benzodiazepine, barbiturates, and opiates except for false positive tests due to medications) on day of neuropsychological testing or fMRI studies; (7) pregnancy (to be verified by urine pregnancy test in women of child-bearing age); (8) inability to read at an 8th-grade level (to be verified by the Wechsler Test of Adult Reading); (9) other contraindications for MRI studies, such as metallic or electronic implants in the body (e.g., pacemaker, surgical clips, or pumps), or severe claustrophobia.

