### Baseline assessments

We will first explain the study to each subject and obtain oral and written consent. The study design, experiments, and consent forms were approved by the institutional review board of the University of Hawaii at Manoa (CHS#20523). A detailed medical and drug use history and physical and neuropsychiatric evaluations will be performed, along with screening blood tests to assess general health, including complete blood cell count, chemistry panel, thyroid function tests, hepatitis C and HIV serology. An electrocardiogram will be obtained to screen for significant cardiac abnormalities; subjects will be referred for further cardiac evaluations should significant abnormalities be found. Psychiatric and quality-of-life evaluations will be additionally performed through a battery of questionnaires and self-reported assessments; some will be repeated after training (Table 1).

**Table 1 Tab1:** Questionnaires and interviews

	Outcome measures	Baseline	1 month after training	6 months after training
Hollingshead Four Factor Index [90]	Socioeconomic status; combination of race, ethnicity, occupational status and education level	✓		
Psychiatric assessments				
Symptom Checklist–90–revised	Psychological and emotional distress	✓	✓	✓
Center for Epidemiological Studies–Depression Scale [91]	Depressive symptoms and to rule out possible major depression	✓	✓	✓
Substance use assessments				
Substance Abuse Subtle Screening Inventory-3 [92]	Identification of individuals with a high probability of having a substance use disorder	✓	✓	✓
Urine toxicology	Substance usage	✓	✓	✓
Quality-of-life assessments				
Independent Activity of Daily Living [93]	Ability to carry out daily functions	✓	✓	✓
Behavior Rating Inventory of Executive Function–Adult Version	Executive function	✓	✓	✓
Pittsburgh Sleep Quality Index [94], Epworth Sleepiness Scale [95]	General level of daytime sleepiness	✓	✓	✓
PROMIS®	Global health status and pain intensity, interference and behavior	✓	✓	✓
Medical Outcomes Study HIV Health Survey [96]	Health status for HIV-positive patients	✓	✓	✓
World Health Organization Quality of Life [97]	Well-being and quality of life	✓	✓	✓
Biospecimens				
Blood	DNA and genotyping	✓		
Blood and serum	Cytokines and monoamines and neurometabolite measurements	✓	✓	✓
Cerebrospinal fluid	Cytokines monoamines and neurometabolite measurements	✓	✓	

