### Statistical analysis

All analyses will be performed using SAS, using repeated-measures analysis of variance (ANOVA) as the primary model (co-varied for age and sex). The baseline (initial) values of all key variables will be tested for normality prior to analysis. Appropriate transformations (or non-parametric tests) will be used as necessary. The statistical significance will be determined using a modified Bonferroni procedure for multiple tests [71]. The procedure will have a type I error probability equal to 0.05 for independent tests.

Neurocognitive assessments will be tested using appropriately constructed contrasts within a 2 × 2 repeated-measures ANOVA model. HIV status (and HAND status for subgroup analyses) and training condition (adaptive versus fixed) will be across-subjects variables, and time (baseline, 1-month, 6-months) will be within-subject variables. Analyses will be co-varied for subject age, sex, and other co-variates as needed (e.g., depression scores). Subjects trained in both the adaptive and fixed training will have the training condition as a within-subject variable.

The fMRI time series will be analyzed using Statistical Parametric Mapping software (SPM8, Welcome Department of Cognitive Neurology, UK). After spatial normalization and smoothing, maps of brain activation and differential changes in activation (repeat − baseline) will be calculated for each subject and task, using a fixed-effects model with a block design. In a subsequent random-effects analysis, differences between groups on BOLD signal changes will be evaluated for each task (*t* tests or ANOVA). Statistical significance will be based on cluster-level significance at *P* < 0.05 corrected for multiple comparisons (voxel-level threshold *P* < 0.05, cluster size >100 voxels). Additionally, we will extract regional percentage BOLD-fMRI signals from cubic regions of interest (0.729 cm^3^) centered at cluster maxima, using a customized program written in Matlab. The extracted data will be imported into SAS, where a repeated-measures ANOVA model will be run to confirm and further evaluate the statistical parametric mapping findings.

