For the genetic study, we will first determine the Hardy–Weinberg equilibrium for both allelic and genotype frequencies of the *LXM1A* gene in our cohort. To minimize the number of correlations, we will use repeated-measures ANOVA to select cognitive variables and extracted fMRI data that show changes from baseline to 6 months after CWMT (adaptive versus active control). We will assess the relationship of these variables with the *LMX1A* genotypes and with cerebrospinal fluid markers using ANCOVA. Repeated measure ANCOVAs and multivariate ANCOVAs will also be utilized.

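### The genotype contrast and the Hardy–Weinberg check pool participants of any ethnicity, and adjustment for ancestry is possible under the plan but not planned

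*Protocol article*

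**What the plan says.** Under Participants, HIV-positive subjects may be "men or women of any ethnicity, ages ≥ 18 years and able to provide informed consent" and seronegative subjects "men or women of any ethnicity, ages ≥ 18 years and able to give informed consent". Evaluation takes place at one centre, the "UH-QMC MR Research Center at the Queen’s Medical Center in Honolulu, Hawaii".

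The genetic paragraph of Statistical analysis starts from the study cohort: "we will first determine the Hardy–Weinberg equilibrium for both allelic and genotype frequencies". It mentions no split by ancestry. Cognitive and fMRI variables that change between baseline and 6 months are then related to genotype by ANCOVA, and that paragraph names no covariates.

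The opening of the same section sets age and sex as covariates for the primary model. The neurocognitive paragraph adds: "Analyses will be co-varied for subject age, sex, and other co-variates as needed (e.g., depression scores".

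Under Methods/design, the HIV-positive and seronegative groups "will be matched by age, sex, education, socioeconomic status, and cognitive status", followed by an open reference to other covariates. Under Participant randomization, the stratification variables are age, sex and severity of cognitive deficit.

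Race and ethnicity appear once, in Table 1, where the socioeconomic index is described as "Socioeconomic status; combination of race, ethnicity, occupational status and education level".

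**The concern.** Training is randomised and genotype is not. Randomisation therefore protects adaptive versus control training, but not TT(AA) versus C(G)-carriers. If ancestry groups differ both in allele frequency and in average gain, the genotype groups differ in ancestry mix, and part of any genotype difference is an ancestry difference.

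The equilibrium check needs less to go wrong. A difference in allele frequency alone produces a shortage of heterozygotes when populations are pooled, even if each is in equilibrium and the genotyping is sound.

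Aim 3 is one of three major aims, and the Discussion presents it as a possible route to personalised treatment. The Dissemination plan includes genotype effects in the interim paper. Under the named model, a positive result could not be separated from ancestry.

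**Working it through.** **The plan's own figures.** The protocol gives no sample size or power for the genotype contrast. Its only calculation is for pre-post change: effect size 0.7 needs about 17 subjects and 0.58 needs 26. Both reproduce with a paired formula: ((1.96 + 0.84)/0.7)² = 16, or 17 with unrounded quantiles and rounding up; the exact paired t gives 26 for 0.58. This point does not depend on them.

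**Inputs.** From the protocol: 102 subjects expected at 1 month and 40 + 42 = 82 at 6 months; alpha 0.05. Assumed, because the protocol gives none: two ancestry groups A and B, each in equilibrium; T-allele frequencies 0.4/0.6 or 0.2/0.6; group B gains 0.3, 0.5 or 0.8 SD more; no true genotype effect.

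**Spurious genotype difference (equal groups).** It equals δ × [P(B | TT) − P(B | C-carrier)].

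- 0.4/0.6: 0.36/(0.16 + 0.36) − 0.64/(0.84 + 0.64) = 0.692 − 0.432 = 0.26. For δ = 0.3, 0.5, 0.8 the bias is 0.08, 0.13, 0.21 SD.
- 0.2/0.6: 0.36/(0.04 + 0.36) − 0.64/(0.96 + 0.64) = 0.90 − 0.40 = 0.50. The bias is 0.15, 0.25, 0.40 SD.

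**False-positive rate, genotype main effect on gain.** Simulation, n = 102, equal groups, 6,000 runs per setting (repeat runs agreed to about one percentage point):

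| T frequency | δ = 0.3 | δ = 0.5 | δ = 0.8 |
|---|---|---|---|
| 0.4/0.6 | 6.5 % | 8.6 % | 13.7 % |
| 0.2/0.6 | 9.5 % | 15.6 % | 32.8 % |

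With an ancestry term in the model the rate is 4.8–5.3 %.

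Hand check of the largest cell: the TT share is (0.04 + 0.36)/2 = 0.20, so about 20.4 TT and 81.6 others. The residual variance is 1 + 0.8² × (0.2 × 0.09 + 0.8 × 0.24) = 1.134, SD 1.065. The standard error is 1.065 × √(1/20.4 + 1/81.6) = 0.264. Then 0.40/0.264 = 1.52, and P(Z > 1.96 − 1.52) is about 33 %.

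**Sensitivity.** With an 80/20 split, n = 102 and δ = 0.5, the rates are 6.7 % (0.4/0.6) and 13.7 % (0.2/0.6). At n = 82 with equal groups, the largest cell falls to about 27 %.

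**Genotype-by-training interaction.** Because training is randomised, the ancestry mix within a genotype is the same in both arms on average. An ancestry main effect on gain therefore cancels, and the rate stays near 5 % (4.6–5.7 %). If ancestry instead modifies the training effect by δ, the bias is again 0.26δ or 0.50δ. The standard error is about twice as large, since each genotype group is split between two arms, and the rate reaches at most about 11 %.

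**Pooled Hardy–Weinberg test.** The heterozygote deficit is F = ((p₁ − p₂)/2)² / (p̄(1 − p̄)), and the 1-df chi-square has non-centrality about nF².

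- 0.4/0.6: F = 0.01/0.25 = 0.04; 102 × 0.04² = 0.16; failure about 7 %.
- 0.2/0.6: F = 0.04/0.24 = 0.167; 102 × 0.167² = 2.8; failure about 39 %.

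Smaller n or unequal groups lower these rates, towards the nominal 5 % for the narrow frequency gap.

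**The case against.** The strongest reply is that this is an unstated detail. The genetic paragraph says only ANCOVA, the covariate clause elsewhere is open, and the covariate set of a secondary genetic model is often left to a fuller plan. Part of that stands. A reader might infer that the plan rules out ancestry adjustment; it does not. But the article does name its covariates, and ancestry is not among them. A confounder added only if it seems needed is weak protection for a genetic association. The clause also does nothing for the equilibrium check.

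A reader might infer that a failed equilibrium check would cause sound genotypes to be discarded. The protocol attaches no consequence to the check, so the harm is limited to a misleading result.

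Matching includes socioeconomic status, whose index mentions race and ethnicity, and the matching list is open. That matching is between HIV-positive and seronegative groups, however, and does not balance genotype groups.

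The numbers rest wholly on assumptions. The 33 % figure needs a wide frequency gap, equal groups and a gain difference of 0.8 SD, which is larger than the 0.7 pilot effect used for sample size. The simulation also tests one outcome and ignores the planned modified Bonferroni procedure. These limits are fair, and so is the observation that the protocol does not fix whether genotype is tested as a main effect on gain or as a modifier of training. Under the second reading the inflation is much smaller.

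**Conclusion.** The point holds in a limited form. The plan pools participants of any ethnicity for a non-randomised contrast, and ancestry adjustment is permitted but not planned. A false genotype effect needs both an allele-frequency difference and a difference in gain or in response to training; a false equilibrium failure needs only the first.

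Under the assumed inputs the false-positive rate is about 6–33 % for a genotype main effect and about 5–11 % for the interaction, with pooled equilibrium failure in about 5–40 % of trials. The true size cannot be known from the protocol and could be negligible. It would be wrong to read this as a threat to the trial's main result: genotype is a secondary contrast, and the randomised training comparison is untouched. The change is worth making because it costs little.

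**What to change.** - Add the race/ethnicity group recorded at baseline as a covariate in every genotype model. Where genotype-by-training is tested, add its interaction with training as well.
- Run the Hardy–Weinberg check within each group of adequate size, and report genotype counts by group.
- Report the genotype effect in the largest group as a sensitivity analysis.
- Confirm that race and ethnicity are stored as separate items, since Table 1 lists them only within the socioeconomic index.

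The cost is a few degrees of freedom and one extra table; no new data are needed if the items are held separately. Two limits remain: the equilibrium test has little power in small groups, and self-reported groups are coarse, so some confounding can persist.

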## Dissemination plan

At the completion of this trial, we plan to submit several manuscripts to peer-reviewed journals including;‘Neural correlates of adaptive working memory training in HIV patients’: this paper will report on the interim findings from the primary outcome measures, including improvements on working memory performance and neural efficiencies, 1 month and 6 months after the adaptive version of CWMT, to assess the gain and maintenance of working memory improvements after training. Some of the secondary contrast results, including scoring on the Behavior Rating Inventory of Executive Function–Adult Version and *LMX1A* genotype effects, will also be reported. These findings may lead to a larger study to validate whether CWMT can be used as an adjunctive therapy for HAND.‘Computerized working memory training in HIV patients: a double-blind active control study’: this paper will be written at the completion of subject enrollments. We will compare the effects of adaptive versus fixed low level of CWMT on the primary outcome measures, at 1 month and 6 months after training compared with baseline assessments. This will provide further evidence of whether CWMT is effective for working memory and attention deficits in HIV patients.This paper will also report on the findings after the double-blind active control study to evaluate the efficacy of CWMT on the secondary outcome measures, including scores on the the Center for Epidemiological Studies–Depression Scale, Revised, and the Symptom Checklist–90–revised, and ability to conduct activities of daily living (Independent Activity of Daily Living assessment and the Behavior Rating Inventory of Executive Function–Adult Version) before and after CWMT.This paper will report on possible improvements in cerebrospinal fluid neuroinflammatory proteins (chemokines and cytokines) and neurochemicals (dopamine and serotonergic levels and their metabolites) after CWMT. Since only half of the participants might consent to the lumbar punctures, we may need to combine results from the adaptive training group and the fix-low-level training group to evaluate the training effects on these cerebrospinal fluid measurements.

We plan to submit our first manuscript on the interim findings before the end of the project in 2015, and the other three papers in 2016 or 2017. The findings will also be presented and discussed at international conferences and workshops, as well as at local symposia to our community healthcare providers.

## Discussion

Cogmed Working Memory Training® may be a useful adjunctive treatment for HAND in HIV-positive patients who are receiving combined antiretroviral therapy. Since CWMT is non-invasive and can be accessed from any computer via the internet, this safe intervention is easily accessible and costs less than typical pharmacological treatments. Furthermore, the proposed work may provide direct and immediate novel data on the long-term maintenance effect of adaptive working memory training, and insight into how the brain and the neural networks involved in working memory and attention may be modified by the training.

The proposed research has several innovative aspects. (1) We will evaluate a new, non-invasive approach to improve cognitive function in HIV-positive subjects. Except for a single recent report of a pilot study of ‘internet-based cognitive stimulation’ (using SmartBrain©) [72], the proposed intervention with CWMT is, to our knowledge, the first to evaluate whether working memory and other cognitive domains can be improved in HIV patients. (2) This will, to our knowledge, be the first study to assess neural plasticity of cognitive training in HIV patients. We will evaluate the neural correlates of the cognitive improvements associated with the intervention, using fMRI techniques. (3) We will genotype subjects to determine whether individuals with the TT(AA) alleles for the *LXMI1A* gene perform better at working memory training. This may pave the way for personalized treatments in the future. (4) Further insights will be derived from studying the relationships between neuroinflammation and brain function (correlations among neuropsychological test scores, working memory performance from the CWMT program, and cerebrospinal fluid cytokines or chemokines). Our approach will provide unique insights into how the brain changes after cognitive training. If successful, the study could lead to a larger intervention study to determine whether working memory training may prevent or improve behavioral and cognitive problems that affect HIV-infected patients. Training the brain might be analogous to physical exercise to prevent cardiovascular diseases, and lead to a new era of prevention for brain disorders.

### Expected findings

#### Gain in working memory performance and transfer of gain to ‘near’ or ‘far’ transfer tasks (Aim 1)

HIV-positive subjects commonly have working memory deficits [3, 23–29, 41–43]. Since working memory is needed to maintain focus on tasks, deficits in working memory may negatively affect many other cognitive domains, and result in HAND. Prior studies of CWMT showed that the program enhanced performance not only on trained working memory tasks, but also on some non-trained visuospatial and non-trained complex reasoning tasks, including executive function [73]. Therefore, we aim to evaluate the efficacy of CWMT on cognitive performance in our subjects.

We hypothesize that all subjects will show improved working memory after Cogmed® RM training (adaptive training > low fixed level ‘active control’ training), both at 1 month and at 6 months after cessation of training. In addition, not only will adaptive CWMT will lead to greater improvements than active control training on the trained tasks, but the gain will transfer to non-trained tasks that require similar working memory processes, including near-transfer tasks (e.g., digit span and spatial span) and far-transfer tasks (e.g., verbal learning, logical memory, short-term memory, and recognition memory). Lastly, we expect that the gain will be greater in subjects with normal cognition (regardless of HIV status) than in those with cognitive deficits (e.g., HAND or HAND-equivalent).

